### Randomization and allocation

The computer-generated randomized lists were drawn up by an independent biostatistics expert before the beginning of the study, using a permuted block design. Biostatistics will employ the SAS 9.4 statistical software PLAN procedure statement on a computer, specifying a seed, to generate randomized treatment assignments for sample subjects. The allocation will be implemented automatically in the electronic case report form (REDCap 10.6.9—© 2024 Vanderbilt University, USA). Allocation concealment will be ensured, as the anesthesiologist will assign the patient to the study group only upon the patient’s arrival in the operating room, ensuring that withdrawal of informed consent has not occurred, and after all baseline measurements will be completed.

### Masking

Trial participants will be blinded to group assignment. Assessments regarding study outcomes will be conducted by an assessor blind to treatment allocation, ensured by concealment of group allocation in the REDCap system to outcome assessor. The assessor will go through a profound assessment training program. Due to the necessity of data collection during intervention, investigators occupied for data collection could not be blinded to allocation, but are strongly inculcated not to disclose the allocation status of the participant at the follow-up assessments. Data analysts can analyze data only after study completion without having access to information about the allocation.

Unblinding to study participants will happen only after the study completion and at participants’ request.

### End of follow-up

Patients enrolled will be followed up until postoperative day 28, hospital discharge, or death, whichever comes first.

### Study endpoints

Given the high sensitivity and specificity of SpO_2_/FiO_2_ in diagnosing acute lung injury without the need for repeated blood sampling [29], we consider it to be a suitable alternative to PaO_2_/FiO_2_. The primary endpoint is time-weighted average SpO_2_/FiO_2_ ratio during the initial post-extubation hour. We first calculated the SpO_2_/FiO_2_ ratio every 15 min during the initial post-extubation hour, and then averaged all SpO_2_/FiO_2_ ratios weighted by measurement interval. Adequate waveform and proper oximeter placement will be confirmed during the initial post-extubation hour. Oxygen flow will be adjusted to maintain pulse oximetry between 92 and 97% during the initial post-extubation hour and ensuring stability for at least 5 min before measurement at each time point. The relationship between oxygen flow and estimated inspired oxygen concentration through different oxygen delivery devices is listed in the Additional file 2.

The secondary endpoints include:Respiratory failure by post-extubation day 7No respiratory failure: SpO_2_ ≥ 90% after breathing ambient air for 10 min (excluding hypoventilation)Mild respiratory failure: SpO2 < 90% or PaO2 < 60 mmHg after breathing ambient air for 10 min (excluding hypoventilation) and corrected with 1–3 L/min with a nasal cannulaModerate respiratory failure: SpO2 < 90% or PaO2 < 60 mmHg despite a 3 L/min oxygen supply with a nasal cannula (excluding hypoventilation) and corrected with an oxygen supply from 4 to 10 L/min with a face maskSevere respiratory failure: SpO2 < 90% or PaO2 < 60 mmHg despite a 10 L/min oxygen supply with a face mask (excluding hypoventilation) and corrected with an oxygen supply > 10 L/min with a high-flow face mask or with non-invasive ventilation or with high-flow nasal oxygen therapy or with invasive mechanical ventilationSeverity of postoperative pulmonary complications by postoperative day 7, scored on an ordinal scale ranging from 0 to 5, using a modified definition of pulmonary complications [10]Grade 0: No symptoms or signalsGrade 1: One of the following: dry cough, abnormal lung findings and temperature 37.5 °C or higher with normal chest radiograph, or dyspnea without other documented causeGrade 2: Two of the following: productive cough, bronchospasm, hypoxemia (SpO2 90%) at room air, atelectasis with gross radiological confirmation (concordance of 2 independent experts) plus either temperature higher than 37.5 °C, or abnormal lung findings, hypercarbia (PaCO2 > 50 mmHg) requiring treatmentGrade 3: One of the following: pleural effusion resulting in thoracentesis, pneumonia, pneumothorax, extended noninvasive ventilation or high-flow nasal cannula, or reintubation lasting less than 48 hGrade 4: Reintubation or invasive mechanical ventilation for 48 h or moreGrade 5: Death before hospital dischargeInvasive mechanical ventilation (IMV) days in ICU by postoperative day 7Duration of invasive mechanical ventilation by postoperative day 7, initiated from ICUadmission.Use of high-flow nasal cannula or non-invasive ventilation by postoperative day 7.Use of new invasive mechanical ventilation by postoperative day 7.No ventilatory support days by postoperative day 7.No ventilatory support days are defined as days without invasive mechanical ventilation,high-flow nasal cannula, and non-invasive ventilation.In-hospital mortalityDeath occurred during hospital stay, time frame from the day of surgery up to hospitaldischarge or death, maximum censoring at day 28 after surgery.ICU length of stayDays since surgery until ICU discharge. The censoring will be performed at day 28 aftersurgery. Patients dying before leaving the ICU were censored as not discharged from ICU atday 28 after surgery.Length of hospital stayDays since surgery until hospital discharge. The censoring was performed at 28 days. Patientsdying before leaving the hospital were censored as not discharged from hospital at day 28.Adverse events by postoperative day 7:Use of high-dose vasopressors (> 1 µg/kg/min of norepinephrine)Postoperative barotraumaDefined as the presence of radiological evidence suggesting pneumothorax, mediastinal emphysema, new-onset pulmonary emphysema, or subcutaneous emphysema.Reoperation before the 12th postoperative hour

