### Intervention

Mechanical ventilation is performed during general anesthesia and intensive care unit (ICU) on volume-controlled mode. All patients are ventilated with low tidal volumes (6–8 mL/kg of predicted body weight) before and after CPB; ventilation is interrupted during CPB. The predicted body weight is calculated with the formula: 50 + 0.91*(Height in cm − 152.4) in men and 45.5 + 0.91*(height in cm − 152.4) in women. The respiratory rate will be adjusted before and after CPB by the anesthesiologist and/or intensivist to maintain end-tidal CO_2_ partial pressure between 35 and 45 mmHg. The lowest fraction of inspired oxygen (FiO_2_) will be targeted in both groups to maintain SpO_2_ ≥ 96%. The inspiratory to expiratory ratio (I:E) is set at 1:2. Positive end-expiratory pressure (PEEP) is set according to low PEEP/FiO_2_ table for ARDS [26] before and after CPB (Table 1). During sternal sawing, PEEP is temporarily set to 0 cmH_2_O to prevent pleural injury. No additional recruitment maneuvers are performed in both groups.

**Table 1 Tab1:** Low PEEP/FiO_2_ table

FiO_2_, %	30	40	40	50	50	60	70	70	70	80	90	90	90	100
PEEP, cmH_2_O	5	5	8	8	10	10	10	12	14	14	14	16	18	18–24

The intervention timeframe commences at randomization and concludes at endotracheal extubation, postoperative day 7, or death, whichever occurs first (i.e., during intraoperative and invasive mechanical ventilation in ICU). In the event of reintubation within postoperative day 7, patients will resume the intervention based on their assigned group.

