#### Postoperative variables

Gas exchange parameters, mechanical ventilation parameters, and respiratory mechanics will be recorded within 10 min, 2 h, and 4 h after ICU admission. Use of rescue therapy will also be recorded during invasive mechanical ventilation in postoperative days. For patients allocated to the experimental strategy, total duration of sigh breaths during the postoperative period, hemodynamic variables, and any interruption of sigh breaths will be documented.

For outcome assessments, SpO_2_/FiO_2_ will be assessed during the initial post-extubation hour, measured every 15 min. Then, patients are visited, twice a day, every postoperative day until postoperative day 7, in order to assess the presence of PPCs or other secondary endpoints. Hospital mortality, length of hospital stay, and length of ICU stay will be assessed upon hospital discharge, death, or postoperative day 28, whichever occurred first. The need for supplemental oxygen will be evaluated at each visit by measuring SpO_2_ and/or PaO_2_ after 10 min of breathing room air. Lung auscultation and daily symptoms of cough and expectoration will also be assessed at each visit. A daily chest X-ray will be prescribed during ICU stay. In the surgical ward, a chest X-ray will be prescribed at the discretion of the attending physician. A chest CT scan will be conducted between the third and fifth postoperative day.

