### Sample size and power

The study determined a sample size of 192 patients (96 per group) with a 5% dropout rate and a *P* value of 0.05 to achieve 90% power in detecting a 10% increase in time-weighted average SpO_2_/FiO_2_ during the initial post-extubation hour in the experiment strategy group, compared to the control group. The control group’s mean time-weighted average SpO_2_/FiO_2_ was estimated to be 294 with a standard deviation of 60, based on previous research [30], and the 10% difference between groups was determined from previous work showing that a decrease of 10% from baseline in PaO_2_/FiO_2_ was clinically meaningful in lung injury induced by ventilatory strategies [31–33]. A dropout rate of 5% was deemed acceptable for informed consent withdrawals post-enrollment.

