The time-weighted average SpO_2_/FiO_2_ ratio will be compared as continuous variable. And treatment effects of primary outcome will also be analyzed according to the following subgroups: (1) age; (2) duration of cardiopulmonary bypass; (3) preoperative pathological chest image; (4) red cell transfusion during surgery. For secondary outcomes, the scores of pulmonary complications and severity of respiratory failure will be analyzed through Mann–Whitney *U* tests and multivariable ordinal logistic regression by estimating the common odds ratio for a shift in the direction of a better outcome on the modified scale. The proportion of other secondary endpoints (use of high-flow nasal cannula or non-invasive ventilation, use of new invasive mechanical ventilation, in-hospital mortality, adverse events) will be compared between the groups. Non-ventilatory support days and invasive mechanical ventilation days by postoperative day 7 will be compared between groups as continuous variables. Multiple comparison corrections will be performed for non-independent outcomes. The duration of ICU and hospital stay was compared using Kaplan–Meier curves and log-rank tests. The censoring was performed at postoperative day 28, and the time to event was the time from surgery end to ICU and hospital discharge. Patients who died before leaving the ICU or hospital were censored as nondischarged at day 28. A 2-sided *P* value < 0.05 was considered statistically significant.

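### Postoperative barotrauma counts any radiological air, including air left by the operation, so the safety comparison between arms is pulled toward no difference

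*Protocol article*

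**What the plan says.** Among the adverse events to postoperative day 7, the Study endpoints section defines barotrauma as "the presence of radiological evidence suggesting pneumothorax, mediastinal emphysema, new-onset pulmonary emphysema, or subcutaneous emphysema". Only the third of these four items carries a novelty condition.

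In the same section, grade 3 of the pulmonary complication scale reads "One of the following: pleural effusion resulting in thoracentesis, pneumonia, pneumothorax, extended noninvasive ventilation or high-flow nasal cannula", with short reintubation as the last alternative. Pleural effusion must have led to a procedure; pneumothorax stands without any condition.

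On imaging, the Postoperative variables section prescribes a daily chest X-ray in the ICU and adds: "A chest CT scan will be conducted between the third and fifth postoperative day". No clinical trigger is attached to the CT, and both kinds of imaging fall within the seven-day window.

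On the source of air, the eligibility criteria require on-pump surgery with aortic cross-clamp, and the experimental strategy is timed around opening and closing the chest. The Intervention section states: "During sternal sawing, PEEP is temporarily set to 0 cmH_2_O to prevent pleural injury".

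The Statistical analysis section compares adverse-event proportions between the arms.

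**The concern.** Air can reach the pleura, mediastinum or chest wall through the operation as well as through the ventilator. The written definition does not separate the two. Read literally, a patient with an uneventful course and a trace of mediastinal air on the day-4 CT is a barotrauma case.

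This matters because the sighs raise plateau pressure to 35 or 40 cmH2O, the Background names safety as something the trial tests, and barotrauma is one of only three listed adverse-event endpoints. Surgical air arises in both arms alike, so it adds false positives that do not depend on allocation. These leave the type I error alone but push the comparison toward no difference, whether the true effect is harm or benefit. With no data monitoring committee, this between-arm comparison is a main place where such harm would be seen.

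**Working it through.** **The plan's own figure.** The protocol's only sample-size figure is for the primary endpoint: "The study determined a sample size of 192 patients (96 per group) with a 5% dropout rate", "to achieve 90% power in detecting a 10% increase in time-weighted average SpO_2_/FiO_2_ during the initial post-extubation hour", with a control mean that "was estimated to be 294 with a standard deviation of 60". The difference is 0.10 × 294 = 29.4. The normal formula gives 2 × (1.960 + 1.282)² × 60² / 29.4² = 87.5, so 88 per arm; the exact t-test gives 89. Dividing 89 by 0.95 gives 94 per arm, 188 in total, close to the stated 192. The figure is sound, but it says nothing about barotrauma, for which the protocol gives no rate or power.

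**Inputs for barotrauma.**
- 96 per arm (Sample size and power).
- Significance rule: "A 2-sided *P* value < 0.05 was considered statistically significant".
- Assumed: true ventilator-related risks of 2% (control) and 10% (sigh).
- Assumed: a share b of each arm with radiological air from the operation, independent of ventilator-related air.

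**Formulas.** Observed risk = b + (1-b) × true risk. The observed risk difference is therefore (1-b) × the true difference. The observed risk ratio moves toward 1 for any b above 0.

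Example, b=20%: control 0.20 + 0.80 × 0.02 = 21.6%; sigh 0.20 + 0.80 × 0.10 = 28.0%; difference 6.4 points; ratio 28.0/21.6 = 1.30.

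| b | Control | Sigh | Difference (points) | Risk ratio | Exact Fisher power |
|---|---|---|---|---|---|
| 0 | 2.0% | 10.0% | 8.0 | 5.0 | about 56% |
| 5% | 6.9% | 14.5% | 7.6 | 2.10 | about 31% |
| 10% | 11.8% | 19.0% | 7.2 | 1.61 | about 22% |
| 20% | 21.6% | 28.0% | 6.4 | 1.30 | about 14% |
| 40% | 41.2% | 46.0% | 4.8 | 1.12 | about 8% |

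The difference shrinks slowly while power drops fast, because the added events raise the variance in both arms. A benefit is diluted in the same way: 10% v 2% has a risk ratio of 0.20 at b=0 and 0.62 at b=10%.

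**Pulmonary complication scale.** Only pneumothorax raises the grade here; mediastinal and subcutaneous air do not. Assume control grades 0 to 5 of 35/20/25/12/6/2%, a true common odds ratio of 2.0 for a better outcome, and a share b of grades 0 to 2 moved to grade 3 in both arms. Simulated Mann-Whitney power is about 75% at b=0, 71% at 2%, 68% at 5%, 61% at 10% and 48% at 20%. If residual pneumothorax is rare, the loss is small.

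**The case against.** **The size is assumed.** This stands. The protocol gives no frequency for surgical air on film or CT. Setting PEEP to zero at sternal sawing is a precaution against pleural injury and does not show that injury is common. Only the direction follows from the text. Even so, a 5% background takes away nearly half the power in the example.

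**Both arms are treated alike, the assessor is blinded and trained, and causality is reviewed.** The first two parts are true and protect against bias in favour of one arm. They do not prevent dilution, which is what equal false positives produce. The causality review under Oversight and monitoring concerns adverse-event handling and stopping the intervention; it changes neither endpoint definition.

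**The endpoint is weak anyway.** This partly stands. Even with no surgical air, power is about 56% for 2% v 10%, and about 16% for 2% v 6%. A reader might infer that this wording would make the trial wrongly show sighs to be safe. The documents do not support that: a non-significant result on an unpowered item does not establish safety under any definition, and the Discussion presents the trial as a test of feasibility and preliminary efficacy.

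**The complication scale makes no claim about cause.** This stands. A reader might infer that grade 3 also scores surgical air as ventilator harm. It is a complication score, modified from a published one and chosen partly for comparability with earlier studies. Excluding pneumothorax from it outright would weaken that comparability.

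**The obvious repair would do damage.** It is tempting to take the first ICU film as baseline and ignore air already on it. Under the experimental strategy, however, sighs are given in the operating room before chest opening and after closure. Air they cause may already be on that film, and dropping it would remove events caused by sighs, which only the experimental arm receives. That would replace even dilution with under-counting of sigh harm.

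**Conclusion.** The point holds for barotrauma. The definition is written out in full, so this is a rule badly fixed and not a detail left to another document. Applied as written, it counts air from the operation and pulls the comparison toward no difference. The reduction of the risk difference by (1-b) is arithmetic and needs only that surgical air be independent of allocation and of ventilator-related air. The fall in power from about 56% to between 31% and 14% for b between 5% and 20% rests on assumed risks of 2% v 10% and on assumed values of b.

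For pneumothorax in grade 3 the effect is smaller and uncertain, and calls for a sensitivity analysis and no change to the scale. The primary endpoint and its sample size are untouched. The change should be made because it is cheap and safety is a stated aim.

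**What to change.** In the Study endpoints section:

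1. Keep the present broad definition, relabelled as radiological air of any cause, and report it by arm as a safety table.
2. Add a stricter barotrauma endpoint: pneumothorax, mediastinal emphysema or subcutaneous emphysema counts only if it is new or enlarging on serial imaging, or led to drainage.
3. Do not use the first ICU film to discard events. Tabulate air present on it by arm; it also stays in the broad count.
4. Tabulate air seen only on the day 3-5 CT separately by arm.
5. Leave the complication scale as it is, and show the grade with and without CT-only pneumothorax as a sensitivity analysis.
6. Have the blinded assessor classify each finding by the same rule in both arms.

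The cost is endpoint wording and one eCRF field, with no added imaging. The stricter count will have fewer events, and stable air from operating-room sighs would fall outside it, which is why the broad and first-film tables must be reported beside it.

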
### Data collection

Study data are managed with a password-protected electronic case report form (REDCap 10.6.9—Copyright 2024 Vanderbilt University, USA). Patient data will be anonymous and coded according to a number. The eCRF includes tools to promote data quality, such as range checks for data values. Data monitoring will be performed by means of queries on the database done by statisticians and analyzed to identify abnormalities and inconsistencies.

All participants will be informed that they will be followed up until postoperative day 28, hospital discharge, or death, whichever occurs first, to ensure the completion of surveys upon consent. Participants choosing to withdraw consent to the study will be encouraged to continue with the follow-up of the trial for the evaluation of efficacy and safety. The reasons and circumstances for discontinuing the study will be recorded.

#### Baseline data

The following baseline data are collected after the patient’s inclusion: gender, age, height, weight, BMI, smoking status, history of COPD or asthma with chronic inhalation therapy, American Society of Anesthesiologists (ASA) score, Euroscore II, lower respiratory tract infection in the past 3 months, abnormal preoperative chest imaging, cardiovascular status (diabetes mellitus, arterial hypertension, dyslipidemia, liver disease, previous acute myocardial infarction, history of cardiac surgery, left ventricular ejection fraction, echocardiographic right ventricular distention defined by a right ventricle/left ventricle ratio > 1, brain natriuretic peptide level, cardiac troponin I level), and status of preoperative creatininemia > 3 mg/dL.

#### Intraoperative variables

During the surgery, the anesthesiologist in charge of the patient will record the following variables: type of surgery (coronary artery bypass graft, valve surgery, aortic surgery, mixed surgery, none of the above), site of vascular graft harvesting (great saphenous vein, mammary artery, radial artery), number of vessels for coronary arterial bypass, CPB duration, aortic cross clamp duration, surgical duration, intraoperative fluid volume (crystalloid and colloid), fluid balance during surgery, use of blood transfusions (include red cell, platelets, or plasma), use of inotropic agents and vasopressors, use of rescue therapy. Gas exchange parameters (arterial blood partial pressure of carbon dioxide, arterial blood partial pressure of oxygen, PaO_2_/FiO_2_), mechanical ventilation parameters (tidal volume, respiratory rate, positive end-expiratory pressure, inspired oxygen fraction, minute ventilation), and respiratory mechanics (peak airway pressure, plateau pressure, driving pressure, respiratory system compliance) will be recorded within 10 min after endotracheal intubation and within 10 min after the conclusion of the surgery.

For patients allocated to the experimental strategy, further details of the experimental intervention will be documented as follows: the total duration of sigh breaths during the intraoperative period. Hemodynamic variables, including heart rate, systolic arterial pressure, diastolic arterial pressure, and mean arterial pressure, will be assessed during the first and second intraoperative sigh breath. Any interruptions in sigh breaths during the intraoperative period will also be documented.

#### Postoperative variables

Gas exchange parameters, mechanical ventilation parameters, and respiratory mechanics will be recorded within 10 min, 2 h, and 4 h after ICU admission. Use of rescue therapy will also be recorded during invasive mechanical ventilation in postoperative days. For patients allocated to the experimental strategy, total duration of sigh breaths during the postoperative period, hemodynamic variables, and any interruption of sigh breaths will be documented.

For outcome assessments, SpO_2_/FiO_2_ will be assessed during the initial post-extubation hour, measured every 15 min. Then, patients are visited, twice a day, every postoperative day until postoperative day 7, in order to assess the presence of PPCs or other secondary endpoints. Hospital mortality, length of hospital stay, and length of ICU stay will be assessed upon hospital discharge, death, or postoperative day 28, whichever occurred first. The need for supplemental oxygen will be evaluated at each visit by measuring SpO_2_ and/or PaO_2_ after 10 min of breathing room air. Lung auscultation and daily symptoms of cough and expectoration will also be assessed at each visit. A daily chest X-ray will be prescribed during ICU stay. In the surgical ward, a chest X-ray will be prescribed at the discretion of the attending physician. A chest CT scan will be conducted between the third and fifth postoperative day.

